### Cost assessment

The direct medical costs of treatment will be described from the institution's perspective. The objective of this cost analysis is to estimate the additional costs related to the intervention and if these additional costs will be overcome by hypothetical cost reduction due to a reduction in the length of hospital stay or other costs related to patient care.

A mixed methodology of micro and macro-costing will be used. Costs related to hospitalization and surgery (operating room time, medical and multidisciplinary consultations, length of hospital stay, ICU stay, and outpatient consultations) will be evaluated. Fixed and variable costs (human resources, material resources, and infrastructure) will be estimated by evaluating the respective unitary values of the institution’s costs. Medicines, medical devices, nutrition, blood, laboratory, and imaging studies will be evaluated by calculating the microcost according to the individual consumption of the patient multiplied by the respective acquisition cost. Operating room time will be measured from patient entry to operating room exit, including anesthesia and surgery. Costs will be presented in the Brazilian Real (R$) (R$ 1.00 = US$0.19; July 31, 2022).

### Institutional resources and infrastructure

The Municipal Hospital Vila Santa Catarina, managed by Einstein in partnership with the public Brazilian health system (SUS), offers all the human and material resources necessary for the project. The hospital has a specialized coloproctology team with operating rooms for the procedures proposed for this project.

### Statistical analysis

An independent author not involved in the recruitment or data collection will perform an intention-to-treat analysis in this superiority controlled trial. Improper application of the rectal tubes will not be excluded from the analysis. The patients will be analyzed according to the group assigned in randomization, even if they drop the intervention or apply only partially (or incorrectly) the rectal stimulation solution. Qualitative variables will be described as absolute counts and percentages. Continuous variables will be described as median and interquartile range. Scores outcomes generated from questionnaires will be evaluated as discrete variables. Differences between groups will be evaluated by the Mann-Whitney test for continuous and discrete variables and Fisher’s exact test or chi-square test for categorical variables. No adjustments per baseline characteristics of the patients are intended.

The investigators will check monthly to ensure the integrity of the data quality, assessing for missing data and invalid field entries. The mean of each variable will be used to replace missing data. The Kolmogorov-Smirnov test will be used to investigate the normality distribution of the variables. For non-normal distribution, a logarithmic transformation will be performed. For sensitivity analysis, the best-worst-case scenario dataset will be generated, assuming all participants lost to follow-up in the intervention group have had a beneficial outcome and all those with missing outcomes in the control group have had a harmful outcome. Then a worst-best-case scenario dataset will be generated assuming all participants lost to follow-up in the intervention group have had a harmful outcome, and all those lost to follow-up in control have had a beneficial outcome. For continuous outcomes, a “beneficial outcome” will be the group mean plus 2 standard deviations of the group mean, and a “harmful outcome” will be the group mean minus 2.

A per-protocol analysis, in which participants who violate the protocol are excluded from the analysis, will be performed as sensitivity analysis to investigate the robustness of the results to protocol deviations.

Statistical analyzes will be performed using the Statistical Package for the Social Sciences, version 18.0 for Windows (SPSS Inc., Chicago, IL, USA).

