### Outcomes

The primary outcome will be as follows: (1) incidence of adynamic ileus (the number of patients needing postoperative nasogastric tube insertion; nausea/vomiting; or intolerance to oral feedings in the first 72 h of the surgery).

Secondary outcomes will be as follows: (1) the time to intestinal transit (time to first evacuation/flatus); (2) time to start feeding; (3) length of hospital stay; (4) grade of colitis (Harig scoring system) [25]; (5) operative complications (during hospitalization); (6) direct costs; (7) stool consistency (Bristol stool scale) [27]; (8) fecal incontinence (Wexner score) [28]; (9) abdominal cramps/pain; (10) number of evacuations per day; and (11) quality of life (SF-36) [29] and low anterior resection syndrome score (LARS) [30]. The secondary outcomes 7 to 11 will be evaluated at every clinical visit during postoperative follow-up. Patients will return after 7–14 days after surgery, followed by 1, 3 months, and 6 months. Patients will be actively investigated for secondary outcomes at each return visit. The relevant questionnaires will be applied at each follow-up visit.

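### The general median, Mann-Whitney and log rule covers direct costs but does not estimate the net cost per patient that the cost objective asks for

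*Protocol article*

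**What the plan says.** In the Protocol article, the Outcomes section lists direct costs as the sixth secondary outcome. Cost assessment gives the viewpoint, "The direct medical costs of treatment will be described from the institution's perspective", and the aim: to "estimate the additional costs related to the intervention and if these additional costs will be overcome by hypothetical cost reduction" from shorter hospital stay or other items of care. Medicines, devices, tests and similar items are costed as "the individual consumption of the patient multiplied by the respective acquisition cost", so each patient has an individual total. The section names no summary statistic, contrast or test for costs.

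The only analysis rules are in Statistical analysis, and they are general:

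- Summary: "Continuous variables will be described as median and interquartile range".
- Comparison: "Differences between groups will be evaluated by the Mann-Whitney test for continuous and discrete variables".
- Transformation: "For non-normal distribution, a logarithmic transformation will be performed".

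Costs are not exempted, and the article mentions neither a mean cost difference nor an interval for one.

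**The concern.** Whether added spending is recovered is a question about the hospital's total bill. The total is the number of patients times the arithmetic mean cost, so the difference in means is the contrast that answers it. A median difference, a rank test and a ratio of geometric means describe other features of the cost distribution and do not convert into net R$ per patient.

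The gap matters here because of where costs and savings fall. The tubes, saline, product and weekly visits are planned for every patient in the intervention arm and shift the whole cost distribution upwards. A saving from avoided ileus comes from a minority in the upper tail, which hardly moves the median, counts only by rank in Mann-Whitney, and is compressed on the log scale. A cost report built on these statistics could call the intervention dearer when it saves money on average, or miss a real saving.

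**Working it through.** **Inputs from the Protocol article.** Ileus 20% vs 2.8%, two-sided alpha 0.05, beta 0.2, 52 per arm (Sample size).

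**The plan's own figure.** With pooled variance and no continuity correction, n = [1.96·√(2·0.114·0.886) + 0.8416·√(0.20·0.80 + 0.028·0.972)]² / 0.172² = (0.881 + 0.364)² / 0.0296 ≈ 52.4. The stated 52 per arm is reproduced to rounding and is not in dispute. It implies about 52 × 0.20 = 10.4 ileus cases in the control arm and 52 × 0.028 = 1.5 in the intervention arm.

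**Mean contrast.** Let c be the added cost per intervention patient and x the extra cost of an ileus case. If ileus is the only source of savings, the mean difference (intervention minus control) is

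D = c − (0.20 − 0.028)·x = c − 0.172·x,

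with break-even at c = 0.172·x.

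**Assumed costs.** The documents give none, so these are illustrative. Base cost is lognormal with median R$5,000 and log SD 0.3, and x = R$15,000, so break-even is c = R$2,580. Trials of 52 per arm were simulated; repeat runs agreed to about one percentage point. Dearer and cheaper mean a two-sided Mann-Whitney p < 0.05 in that direction.

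| Assumption | True mean difference (R$) | Median difference (R$) | Dearer | Cheaper |
|---|---|---|---|---|
| c = 1,000 | 1,000 − 2,580 = −1,580 | about +550 | about 18% | under 1% |
| c = 1,500 | 1,500 − 2,580 = −1,080 | about +1,050 | about 55% | 0% |
| c = 500 | 500 − 2,580 = −2,080 | about +50 | about 2% | about 4% |
| c = 250 | 250 − 2,580 = −2,330 | about −200 | under 1% | about 14% |
| c = 1,000, log SD 0.5 | −1,580 | about +230 | about 3% | about 2% |
| c = 1,000, routine costs also fall by 1,000 | 1,000 − 1,000 − 2,580 = −2,580 | about −450 | about 0% | about 33% |

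The intervention truly saves money in every row. At c = R$1,500 the geometric mean ratio is 1.03, so the log scale also points the wrong way.

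**A second set of assumptions.** Uncomplicated mean cost is 100 units (coefficient of variation 0.2), with a variable ileus excess.

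- c = 20, x = 200: mean difference 20 − 34.4 = −14.4, median difference +14.3, geometric mean ratio 1.00, dearer in 59% of trials and cheaper in none.
- c = 5, x = 200: mean difference 5 − 34.4 = −29.4, yet the saving is detected in only 7%.
- c = 20, x = 50: mean difference 20 − 8.6 = +11.4, median difference +14.9. Both say dearer.

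The log rule does not alter a Mann-Whitney result, since ranks are unchanged. It matters only if costs are summarized or compared on the log scale.

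**The case against.** The case against has four parts.

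1. *Costs have their own section.* It speaks of describing and estimating, states no hypothesis test, and the article is a condensed text; the full plan may treat costs separately. It is true that nowhere is a Mann-Whitney p-value said to decide whether the added cost is recovered, and a reader who infers that goes beyond the text. But the article does fix a rule for continuous variables, costs are such a variable, and the cost section offers no alternative. The point concerns a stated rule that does not fit a stated aim, not a missing detail.

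2. *The size of the problem rests on invented costs.* This stands. Halving the added cost from R$1,000 to R$500 takes the wrong-direction rate from about 18% to about 2%, and a wider cost spread takes it to about 3%. Only a range can be given.

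3. *Savings need not come only from ileus cases.* This also stands. The Background reports, from the earlier trial of efferent-loop stimulation, a stay of 2.5 vs 4.6 days and faster diet acceptance and defecation. If ileus alone explained the 2.1-day difference, each case would add about 2.1 / 0.17 ≈ 12 days, which is hard to square with a control mean of 4.6. If routine costs fall as well, the reversal largely disappears. A reader might infer that the whole saving sits in a few expensive cases; the documents do not say so.

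4. *Much of the remedy is already there.* Analysis by randomized arm is planned, and outpatient consultations, medicines and devices are counted. What is lacking is the mean contrast and its interval.

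**Conclusion.** The mismatch holds: the general rule reaches direct costs, and none of its statistics estimates the net cost per patient that the cost objective seeks. That does not depend on any cost figure.

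The practical consequence does. Under the assumed R$ costs, with a true mean saving throughout, the wrong-direction Mann-Whitney rate runs from about 0% to 55% (59% in the least favourable case of the second set). Where the added cost is small or routine stays also shorten, mean and median agree in sign; where the added cost exceeds the saving, both say dearer.

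A reader might infer that the planned analysis will usually mislead about cost. The documents do not support that, because they give no cost data and their background evidence is compatible with broad savings.

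The change is worth making but not critical. Costs are one of eleven listed secondary outcomes, and the primary outcome, sample size and data collection are unaffected.

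**What to change.** Add to Cost assessment or Statistical analysis wording such as: direct costs are exempt from the general rule for continuous variables; arithmetic mean total cost per patient will be compared between randomized arms in untransformed R$, as a mean difference with a 95% confidence interval (for example by bootstrap); the intervention arm's total includes the rectal stimulation materials and the extra weekly visits; medians and interquartile ranges are given as description only.

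The bootstrap is one acceptable choice among several. The change needs a few lines of wording and a small amount of extra analysis, with no change in sample size. It draws on the patient-level cost data already planned, provided the intervention materials and weekly visits are recorded among them.

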### Study groups

Intervention group (with rectal stimulation): The patient will receive guided instruction in an outpatient setting. The patient will receive the necessary materials, which include 14-French rectal tubes, saline, and a source of soluble prebiotic fibers (fructooligosaccharide) with probiotics (*Lactobacillus acidophilus*, *Lactobacillus rhamnosus*, *Lactobacillus para casei*, *Bifidobacterium lactis*) (Simbioflora®; Brand: Invictus; Manufacturer: Farmoquimica; MS1666370001001 Registry). The patient will apply 500 ml of saline solution with 6 g of Simbioflora® rectally, once daily, for 15 days before the ileostomy reversal surgery. The saline solution vials will have a predetermined volume (500 ml) to guarantee that the patients use the correct volume. The patient will have weekly visits, and the researchers will provide a contact for service at any time to optimize patients’ adherence.

Control group (without rectal stimulus): The patient will be submitted to the ileostomy reversal with no previous rectal stimulus. No placebo will be applied.

In both groups, patients will be instructed to record colic/abdominal pain symptoms, nausea/vomiting, diarrhea, and gas during the 15 days prior to ileostomy closure.

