### Preoperative workup

Before surgery (1 to 3 months prior to surgery), the patients will have a thoracic and abdominal computed tomography (CT) scan and pelvic MRI for routine oncologic evaluation. CT scan will be performed with endovenous and rectal iodinated contrast. In addition, a digital examination and rectoscopy will be performed. Rectoscopy will assess the grade of colitis (Harig scoring system) [25]. During rectoscopy, if there are changes in the mucosa or anastomosis, such as inflammatory areas or suspicious malignancy, biopsies will be performed according to the usual care of all patients with rectal cancer during oncological follow-up. These procedures are already performed for the usual routine service management before ileostomy closure.

All patients will then undergo a standardized preoperative clinical and anesthesiological evaluation.

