### Surgical techniques and surgeons

Five experienced surgeons will perform the procedures (all performed more than 50 ileostomy closures).

Patients will have 8 h of fasting. Infusion of second-generation cephalosporins will be performed intravenously during anesthetic induction before the procedures.

The initial approach (total mesorectal excision with protective ileostomy) will be performed with minimally invasive access (robotic-assisted or laparoscopic) following the following technique:

1—Patient in lithotomy position under spinal anesthesia and sedation; 2—Antisepsis with alcoholic chlorhexidine solution; 3—Asepsis and placement of sterile surgical drapes; 4—Inspection of the cavity for the presence of metastases; 5—Identification, isolation, and sealing of the inferior mesenteric vein at its origin; 6—Left mesocolon detachment from retroperitoneum structures; 7—Access to the retrocavity of the epiplons, and opening of the intercolonepiploic space, with release of the splenic angle; 8—Identification, isolation, and clipping of the inferior mesenteric artery at its origin; 9—Release of left parietocolic gutter; 10—Mesorectal dissection up to the level of the levator ani muscles and posterior section of the rectum; 11—Colorectal anastomosis with Circular Stapler (CDH 29); 12—Construction of a protective ileostomy 30 cm from the ileocecal valve, in loop, with its fixation through a hole created in the right hemiabdomen, through the rectus abdominis muscle, and fixation with Vycryl 3-0; 13—Review of hemostasis; synthesis of aponeurosis and skin; 14—Dressings.

The second surgery (ileostomy reversal) will be performed at least two months after the first surgery, after adjuvant therapy (when indicated), and the following technique will be followed:

1—Patient in lithotomy position under spinal anesthesia and sedation; 2—Antisepsis with alcoholic chlorhexidine solution; 3—Asepsis and placement of sterile surgical drapes; 3—Circular incision around the ileostomy, opening in layers until the release of the ileostomy from the aponeurosis; 4—Barcelona technique anastomosis; 5—Review of hemostasis; synthesis of aponeurosis and skin; 6—Dressings.

A rectoscopy will be performed intraoperatively to assess colitis grade (Harig scoring system) [25].

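### Colitis grade is scored before and after the stimulus on the same scale, but the plan rules out baseline adjustment and so gives up precision on this secondary outcome

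*Protocol article*

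**What the plan says.** Four sections of the Protocol article bear on this.

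- **Preoperative workup.** Before reversal, "Rectoscopy will assess the grade of colitis (Harig scoring system" is named as the scale. The section opens with a time window: "Before surgery (1 to 3 months prior to surgery), the patients will have a thoracic and abdominal computed tomography (CT) scan".
- **Study groups.** The stimulus is given "once daily, for 15 days before the ileostomy reversal surgery".
- **Surgical techniques and surgeons.** At the reversal itself, "A rectoscopy will be performed intraoperatively to assess colitis grade (Harig scoring system" is again the scale.
- **Outcomes.** Colitis grade is the fourth of eleven secondary outcomes, listed without a time point and without mention of change from the first score.

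The Statistical analysis section assigns the Mann-Whitney test to continuous and discrete variables and Fisher's exact or the chi-square test to categorical ones. It then states for the whole trial: "No adjustments per baseline characteristics of the patients are intended". The Randomization section describes blocks only and mentions no stratification factor.

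**The concern.** A pre-treatment measurement of the outcome on the same scale is usually the most useful covariate a trial has. Here it is collected as part of the plan and then set aside by an explicit sentence. This is a stated choice, not a detail left to a separate analysis plan.

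Baseline colitis is balanced by chance alone: allocation is not described as stratified on it, and the analysis does not account for it. Variation between patients that the first grade could explain stays in the error term. Colitis matters to the authors, since the Background gives its amelioration as one of the hypotheses. They also criticise an earlier probiotic trial for probably lacking power on outcomes other than its primary one. At stake is how informative this trial will be on colitis, not whether its test is valid.

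**Working it through.** **The plan's own figure.** The 52 per arm belongs to the primary outcome: 20% against 2.8%, two-sided alpha 0.05, power 80%. With pooled variance and no continuity correction, the mean proportion is (0.20 + 0.028)/2 = 0.114, and

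n = [1.960 × √(2 × 0.114 × 0.886) + 0.842 × √(0.20 × 0.80 + 0.028 × 0.972)]² / 0.172² ≈ 52.4.

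That is 53 after rounding up, and power at 52 is 79.7%. The figure reproduces to within one patient. Nothing below changes it.

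**Order of measurements.** If the 1-to-3-month window covers the rectoscopy, the first grade falls before the 15-day stimulus and the intraoperative grade after it. The first is then a true pre-stimulus baseline.

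**Value of the baseline.** Let r be the correlation between the two grades. In the linear approximation, adjustment multiplies the residual variance by 1 − r², so 52 patients per arm carry the information of 52/(1 − r²). The difference detectable with 80% power is (1.960 + 0.842) × √(2/52) × √(1 − r²) = 0.55 × √(1 − r²), in SD units. Neither r nor a target effect on colitis is in the protocol; both r and the 0.5 SD effect are assumptions.

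| Assumed r | 1 − r² | Equivalent n per arm | Gain in patients | Detectable difference | Power for 0.5 SD |
|---|---|---|---|---|---|
| 0 | 1.00 | 52 | none | 0.55 SD | 72% |
| 0.3 | 0.91 | 57 | 10% | 0.52 SD | 76% |
| 0.5 | 0.75 | 69 | 33% | 0.48 SD | 84% |
| 0.7 | 0.51 | 102 | 96% | 0.39 SD | 95% |

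**Check on an ordinal scale.** The grade is ordinal, so the linear factor is only approximate. A simulation used an invented four-level grade, 52 per arm, 3,000 runs per setting and a latent shift of 0.55 SD. It compared the Mann-Whitney test on the final grade with a rank-based analysis of covariance using the first grade.

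| Latent r | Mann-Whitney, unadjusted | Rank covariance analysis |
|---|---|---|
| 0 | 72% | 72% |
| 0.3 | 72% | 74% |
| 0.5 | 74% | 81% |
| 0.7 | 72% | 90% |

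With no treatment effect, both methods rejected in about 4% to 5% of runs. The pattern matches the linear table: a clear gain at moderate or high correlation, little at 0.3 and none at zero.

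**The case against.** The strongest reply is that this is a matter of efficiency. The unadjusted test is prespecified and keeps its error rate, and colitis is one secondary outcome among eleven. That stands, and it limits the weight of the point. A reader might infer that the result will be biased, or that chance imbalance makes the test untrustworthy. The documents do not support this: under randomisation, chance imbalance is already covered by the test's error rate.

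Other stronger readings also go beyond the text.

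- **That the plan compares only post-stimulus grades and forbids any use of the first one.** The outcome is listed simply as "4) grade of colitis (Harig scoring system) [25", with no time point. The no-adjustment sentence is general, and a change score is neither planned nor expressly excluded.
- **That the first grade is firmly dated 1 to 3 months before surgery.** The window is written for the imaging; the rectoscopy follows in the same paragraph and takes the window only by context. The Preoperative workup section also calls these procedures routine, while Risks and inconveniences counts a rectoscopy before surgery among the study's additional actions.
- **That adjustment has no downside.** The trial is open-label and its randomisation sequence is not concealed. The text does not say that the first grade is scored before allocation is known. If it were scored afterwards, adjusting for it could carry bias into the estimate. Sparse grades can also make a proportional-odds model fit poorly.
- **That the gain is known.** The correlations are assumed. If the two rectoscopies are months apart, or if grades hardly vary, the gain may be small. The simulation used a rank covariance analysis, not the exact methods proposed below, so it supports the direction and rough size only.

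**Conclusion.** The point holds as a loss of precision on colitis grade. The plan collects a same-scale grade that, by context, precedes the stimulus. It then lists only unadjusted tests and states that no baseline adjustment is intended. The comparison remains valid, and the primary analysis and sample size are untouched.

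The illustrative value of adjustment runs from nothing at zero correlation to about 10%, 33% and 96% more patients at assumed correlations of 0.3, 0.5 and 0.7. This rests on three conditions: that the intraoperative grade is the intended endpoint, that the preoperative grade is scored before randomisation, and that the linear factor is a fair guide for an ordinal score. The change is worth making because the data are already planned, but it is an improvement to one secondary analysis and not the correction of an invalid one.

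**What to change.** Replace the no-adjustment sentence in the Statistical analysis section with wording such as:

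> The intraoperative Harig grade will be compared between arms with adjustment for the preoperative Harig grade scored before randomisation (Mann-Whitney test stratified by preoperative grade, i.e. van Elteren, or a proportional-odds model if grades are not too sparse), with the unadjusted test as a supporting analysis. No other baseline adjustment is planned.

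This also settles which of the two grades is the endpoint. The primary ileus test can stay unadjusted: the design rates imply only 52 × (0.20 + 0.028) ≈ 11.9 events.

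The cost is small. No new measurement is needed, provided the first grade is recorded before allocation. The analysis takes slightly more work, sparse preoperative grades may have to be collapsed by a rule set in advance, and a proportional-odds model reports an odds ratio conditional on the starting grade.

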### Sample size

Assuming that the intervention will reduce the adynamic ileus incidence after ileostomy reversal from 20 to 2.8% [12], the estimated sample is 52 patients in each study arm, considering alpha (two-sided) 0.05 and beta 0.2 [24]. Considering that our primary outcome will be a short-term endpoint, evaluated during hospitalization after surgery, we do not expect a significant loss of follow-up for the primary outcome.

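### Filling missing data with the variable's mean cannot work for the yes/no ileus outcome, and for the other outcomes it dilutes the comparison or, if group means are used, inflates false positives

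*Protocol article*

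**What the plan says.** The Statistical analysis section gives one rule for incomplete data: "The mean of each variable will be used to replace missing data". It excepts no type of variable and does not say whether the mean is taken over all patients or within each arm. The best-worst and worst-best datasets come later in the same paragraph and are labelled as sensitivity analysis, so the mean rule governs the main analysis.

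The rule meets three kinds of outcome:

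- **Primary outcome (Outcomes section):** "incidence of adynamic ileus (the number of patients needing postoperative nasogastric tube insertion; nausea/vomiting; or intolerance to oral feedings in the first 72 h". Each patient either has ileus or does not, and the planned test is "Fisher’s exact test or chi-square test for categorical variables".
- **Times, costs and scores:** these are summarised by median and interquartile range, or treated as discrete scores, and compared by the "Mann-Whitney test for continuous and discrete variables".
- **Repeated outcomes:** "The secondary outcomes 7 to 11 will be evaluated at every clinical visit during postoperative follow-up", that is at 7–14 days and at 1, 3 and 6 months.

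On expected loss, the Sample size section says only that "we do not expect a significant loss of follow-up for the primary outcome".

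**The concern.** This is a stated rule, not a detail left for a later analysis plan, and it does not fit the data it governs.

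- **Ileus:** the mean of a yes/no variable is a proportion. It is not a status that a patient can have. If even one status were missing, the analyst would have to improvise after seeing open-label data.
- **Skewed times and costs, ordinal scores:** the mean is not a typical value, as the plan's own use of medians implies. Filled-in values count as if observed, and they form a block of ties in a rank test.
- **Outcomes 7 to 11:** the rule ignores the patient's own earlier visits.

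At stake are an analysis rule that cannot be carried out on the primary outcome, and secondary comparisons that are either diluted or too liberal, depending on which mean is used.

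**Working it through.** **Inputs.** From the Sample size section: 52 per arm, two-sided alpha 0.05, beta 0.2, ileus 20% and 2.8%. The missing fraction m is not in the document; 5%, 10% and 20% per arm are assumed.

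**1. The plan's own figure.** Pooled-variance formula for two proportions, with mean rate (0.20 + 0.028)/2 = 0.114:

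n = [1.960·√(2·0.114·0.886) + 0.842·√(0.20·0.80 + 0.028·0.972)]² / 0.172² = (0.881 + 0.364)² / 0.0296 ≈ 52.4.

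This is 53 when rounded up, against the stated 52; power at 52 per arm is 79.7%. The figure is reproduced and this point does not change it.

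**2. Binary outcome.** The filled-in value would be 0.114 (overall mean), or 0.20 and 0.028 (group means). None is 0 or 1, and none can be added to a 2×2 table of counts.

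**3. Overall mean, other outcomes.** Filling a fraction m of both arms with the same value shrinks a mean difference d to (1−m)d. For d = 0.60 SD: 0.60 × 0.95 = 0.57, 0.60 × 0.90 = 0.54, 0.60 × 0.80 = 0.48. Simulation gave 0.57, 0.54 and 0.49 (at 20%, 10 of 52 values are filled).

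**4. Group mean, other outcomes.** The mean difference is kept, but the computed SD falls by about √(1−m) while the full n is credited. The computed standard error is therefore about (1−m) times the valid one: 0.95, 0.90, 0.80. For a z-type test, type I error = 2[1 − Φ(1.96(1−m))] = 6.3%, 7.8%, 11.7%; the simulated t-test gave 6.4%, 7.2%, 10.8%. The rank test does worse. At 20% missing, 10 × 10 = 100 of the 52 × 52 = 2,704 between-arm pairs compare one filled value with another, and all 100 fall the same way.

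**5. Simulation of the planned Mann-Whitney test.** 52 per arm, 3,000 runs per scenario, missing completely at random. Type I error is shown as normal / log-normal data, in %; power (%) is for normal data with a true shift of 0.60 SD.

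| Assumed missing | Type I, observed only | Type I, overall mean | Type I, group mean | Power, observed only | Power, overall mean |
|---|---|---|---|---|---|
| 5% | 4.5 / 4.9 | 4.6 / 4.6 | 7.2 / 6.9 | 81.7 | 82.9 |
| 10% | 4.8 / 4.8 | 4.7 / 5.7 | 8.6 / 8.9 | 79.8 | 78.4 |
| 20% | 5.2 / 5.4 | 4.7 / 4.8 | 17.9 / 16.1 | 75.5 | 73.2 |

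Simulation error is about 0.4 points for a rate near 5% (√(0.05·0.95/3000)) and about 0.7 points for a power near 80%, so the 1.2-point gap at 5% missing is not a gain. Longer runs (6,000) with group means gave 9.5% and 18.7% at 10% and 20% missing for normal data, and 8.6% and 17.1% for log-normal data. At a shift of 0.56 SD, power with overall-mean filling against observed data was 77.4% against 78.0% at 5% missing, 73.4% against 74.0% at 10%, and 68% against 69% at 20%. For log-normal data the loss was 1–2 points at 5–10% missing and 4 points at 20%.

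**The case against.** The other side has four good arguments.

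- **Which mean.** A reader might infer that the plan multiplies false positives. The text does not support that as it stands. The disputed sentence speaks of the mean of the variable, whereas the extreme-case rule later in the paragraph names the group's mean explicitly. The overall mean is the more natural reading, and under it type I error stays near 5%. The inflation figures are conditional on the other reading, which the text leaves open.
- **How much is missing.** The document gives no rate. With group means and only 2% missing, type I error is about 5.4%; large inflation needs large loss.
- **The primary outcome.** A reader might infer that the primary analysis is invalid. It is not: ileus is assessed within 72 h in hospital, little loss is expected, and with complete data the rule is never used. What stands is that the rule cannot be applied if any status is missing.
- **Safeguards.** A reader might say that the plan offers nothing on loss beyond the sample-size remark. In fact it plans monthly checks for missing data and both extreme-case datasets. These are sensitivity analyses, however, and leave the main result as computed.

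It is also fair that the plan reports no mean difference, so the dilution in step 3 matters mainly through the power of the rank test, where the loss is small.

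**Conclusion.** The rule is wrong as written and should be fixed. It cannot be executed for the yes/no primary outcome, and it clashes with the section's own medians and rank tests.

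On the more natural overall-mean reading the statistical harm is modest: type I error near 5%, a diluted difference, and power equal to or a few points below that of observed data alone, so the filling buys nothing. Only if group means were used would Mann-Whitney type I error rise, to about 7%, 9–10% and 17–18% at 5%, 10% and 20% missing.

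These sizes rest on assumed missing fractions and on data missing completely at random, which is a favourable case for mean filling. The practical effect falls mainly on the questionnaire and functional outcomes followed to 6 months. Severity: should-fix.

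**What to change.** 1. Delete the mean-replacement sentence.
2. State that the main analysis uses patients with an observed outcome, in their randomized arm, with Fisher or chi-square and Mann-Whitney as planned.
3. State that missing ileus status is handled by the already planned best-worst and worst-best datasets, reported as bounds around the intention-to-treat result.
4. For the repeated outcomes 7 to 11, add as a supporting analysis either a mixed model over all visits, or multiple imputation by arm with a model-based estimate that can be pooled. Mann-Whitney tests do not yield an estimate and standard error for the usual combination rules, so multiple imputation should not simply be placed in front of them.

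The cost is a paragraph of wording and slightly more analysis work, with no extra patients or visits. The downside is that the few patients with a missing outcome are left out of the main comparison. That sits less easily with intention-to-treat, which is why the bounds in item 3 should be reported beside it.
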